## Study Termination

The principal investigator and the investigator (IRB-approved and delegated by the principal investigator) may, in consultation with the study sponsor, decide to terminate early or temporarily suspend the clinical study if it is deemed undesirable to continue based on the results collected during the study process. The sponsor may also terminate the study early for safety or administrative reasons. The principal investigator must promptly report this to the IRB and provide detailed reasons for the early termination or suspension.

Reasons for study termination by the sponsor are as follows:

1. Cancellation or suspension of the marketing authorization of the investigational product.
2. The sponsor determines that continuing the study is not medically or ethically justified.
3. Excessive delays in subject recruitment make the study unfeasible.

In the event of early termination or temporary suspension, the investigator must inform the subjects and ensure appropriate actions and follow-up visits are carried out. The investigator must summarize and report the status and results up to the point of termination in the eCRF and provide this information to the sponsor.

# Clinical Study Method

## Overall Study Design

This clinical study is designed as a primary care-based, prospective, multicenter, cluster-randomized, pragmatic clinical trial to confirm the improvement effects on blood glucose, blood pressure, and weight over 24 weeks in patients with Type 2 Diabetes when using ‘Well Check’ with or without investigator-linked management in real-world primary care settings.

Eligible subjects include patients currently being treated with Envlo Tab. or Envlomet SR Tab. for Type 2 Diabetes or those deemed eligible for such treatment by the investigator (responsible physician). Subjects must also be able to use the digital healthcare smartphone application without difficulty.

Due to the practical constraints of primary care settings, where it is challenging to manage test group and control groups separately within the same institution, cluster randomization will be used. Institutions will be randomized as either the test group [institutions managing subjects with the 'Well Check' app in conjunction with the investigator (responsible physician)] or the control group (institutions where subjects use the 'Well Check' app for self-management). The study will be conducted following this setup.

[figure not shown]

Study Subjects

Use of 'Well Check'
for Simple Self-Management

(Control Group Institutions)

Investigator
(Responsible Physician)

Use of 'Well Check'
for Integrated Management
(Study Group Institutions)

Cluster Randomization

Participating Institutions

(Primary Care Institutions)

Figure 1. Clinical Study Design

Data collection for this clinical study will be based on medical records documented during routine clinical visits. Collected data will include demographic information, physical measurements, vital signs, and laboratory test results. There are no mandatory visits, tests, or treatments specified by this study.

However, prospective data collection through follow-up visits will be conducted up to 24 weeks from the baseline registration date.

The planned time points for prospective data collection are baseline (0 days), visit 2 (6 weeks), visit 3 (12 weeks), visit 4 (18 weeks), and visit 5 (24 weeks). Visits 2 and 4 can be optionally collected based on the investigator (responsible physician)'s judgment and allow for telephone follow-ups.

[figure not shown]

Visit 1

(0 days)

Visit 2

(6±2 weeks)

Visit 3

(12±2 weeks)

Visit 4

(18±2 weeks)

Visit 5

(24±2 weeks)

Baseline

Follow-Up Visits

Close-Out Visit (COV)

Figure 2. Clinical Study Flowchart

## Duration of Study

This study is expected to last till December 31, 2026 from the date of IRB approval. For each subject, the data collection period will be up to 24 weeks (6 months), during which the information specified in the study protocol will be collected. However, if circumstances arise that affect the study progress, such as difficulties in subject recruitment, the period may vary.

## Study Procedure and Schedule

### Visit Schedule

There are no mandatory visits, tests, or treatments specified by this study. Data will be prospectively collected using medical records, investigator assessments, and laboratory test results from routine clinical visits. Each investigator will collect predefined information from subjects at baseline and during the follow-up period.

1. **Visit 1 (Baseline, Day 0)**

At the first visit (baseline), the following information will be collected:

- Obtain subject consent and assign subject enrollment number
- Inclusion/Exclusion Criteria Confirmation
- Installation and Hospital Integration of the Digital Healthcare Smartphone Application ‘Well Check’
- Demographic information [initials, gender, age (month and year of birth), pregnancy and breastfeeding status].
- Information on Type 2 Diabetes (Diagnosis date)
- Medical history (Past medical history within 6 months prior to enrollment (excluding the target disease) and current medical history)
- Alcohol/Smoking/Lifestyle information
- Physical measurements (height, weight, BMI)
- Vital signs (systolic/diastolic blood pressure, pulse rate)
- Body composition analysis (include skeletal muscle mass, body fat mass, body fat percentage, muscle mass, waist/hip circumference, body water, intracellular water, extracellular water, extracellular water ratio, abdominal fat percentage, etc.)
- Prior medications (diabetes treatments within 4 weeks prior to enrollment) and concomitant medications (all medications, including diabetes treatments, taken at the time of enrollment).
- Laboratory tests (HbA1c, FPG, Total Cholesterol, LDL-C, HDL-C, Triglyceride, ALT, AST, Creatinine, e GFR, UACR, UGCR, etc.)

1. **Follow-Up Visits**

Follow-up visits will be conducted at 6-week intervals from the first visit (baseline) as Visit 2 (6 weeks ±2 weeks), Visit 3 (12 weeks ±2 weeks), Visit 4 (18 weeks ±2 weeks), and Visit 5 (24 weeks ±2 weeks). Visits 2 and 4 may be optional and data collection can be conducted via phone calls, based on the investigator (responsible physician)’s discretion. During follow-up visits, the following information will be collected:

- Alcohol/Smoking/Lifestyle information
- Physical measurements (weight, BMI)
- Vital signs (systolic/diastolic blood pressure, pulse rate)
- Body composition analysis (include skeletal muscle mass, body fat mass, body fat percentage, muscle mass, waist/hip circumference, body water, intracellular water, extracellular water, extracellular water ratio, abdominal fat percentage, etc.)
- Concomitant medications
- Laboratory tests (HbA1c, FPG, Total Cholesterol, LDL-C, HDL-C, Triglyceride, ALT, AST, Creatinine, e GFR, UACR, UGCR, etc.)
- (End of Study) Well Check User Experience Satisfaction Survey

## Information and Items Collected

1. **Obtaining Written Consent and Assigning Screening Numbers to Study Subjects**

Study subjects are outpatient visitors, and, if necessary, subjects are recruited through voluntary participation via recruitment announcements on the hospital's bulletin board.

Before collecting data related to this study, the investigator must explain the purpose and details of the study to the study subjects through an information sheet and obtain voluntary consent. This consent must include the subject's name, signature, and the signing date.

The date of written consent and Visit 1 (Baseline, Day 0) may differ, but consent must be obtained before participation in the clinical study.

Screening numbers for subjects are automatically assigned in the eCRF upon obtaining consent. Subject numbers are 6 digits and formatted as “AXX-ZZZ”, where:

- “A”: Classification code (A, B)
- “XX”: Institution number (01, 02 -)
- “ZZZ”: Subject number at each institution in the order of consent (001, 002 -)

1. **Inclusion/Exclusion Criteria Confirmation**

Inclusion/Exclusion criteria are confirmed at Visit 1 (Baseline, Day 0) to verify if all inclusion criteria are met and none of the exclusion criteria apply.

1. Installation and Registration of the ‘Well Check’ APP

Subjects enrolled in the study will install the 'Well Check' smartphone application, register, and enter the institution code provided for the study to link it with the hospital.

**[Test Group]**

For the test group, the basic usage of the 'Well Check' smartphone application is recommended as follows. Within the 'Well Check' app, investigators and subjects are encouraged to freely use the features considering the subject's medical condition. If self-recording for chronic disease management such as [Blood Glucose], [Blood Pressure], [Weight], [Medication Records], or regular completion of [Health Education] in 'Well Check' is insufficient, the investigator can encourage self-management and education completion via the messaging feature of 'Well Check.'

1. Visit 1 (Baseline, Day 0)

- Subject: Complete [Basic Questionnaire], [Health Checkup Results], and set [Medication Alarm] in the 'Well Check' application.
- Investigator (Responsible Physician): Enter [Blood Test Results], evaluate [ASCVD risk], and use the linked subject's medical history, lifestyle, and symptoms for consultation in the 'Well Check Doctor Web.'
- See Appendix 6. Provide and guide the “Attachment 6. Well Check User Guide” pamphlet.

1. Visit 2 (Follow-up Visit, 6 weeks) to Visit 5 (Close-out Visit, 24 weeks)

- Subject: Enter [Pre-visit Questionnaire] in the 'Well Check' application during visits.
- Investigator (Responsible Physician): Review and analyze the patient’s self-records (questionnaire, blood glucose, blood pressure, weight, medication records) and recent symptoms and lifestyle (alcohol/smoking/exercise) feedback in the 'Well Check Doctor Web.' Enter [Blood Test Results] (if tested), evaluate [ASCVD risk], and use it during consultations

1. During the Study Period (Visit 1 to Visit 5)

- Subject: Record [Blood Glucose] (at least once daily), [Medication Records] (when taking medication), [Blood Pressure] and [Weight] (at least once weekly) in the 'Well Check' application. Complete [Primary Doctor Messages] education (twice weekly) and use [Health Education].
- Investigator (Responsible Physician): Monitor cautionary patients* in 'Well Check Doctor Web' (once weekly) and send encouragement messages to those who do not measure blood glucose (once monthly)

**An alert is sent to 'Well Check Doctor Web' if the blood glucose level is below 54 mg/dL or above 200 mg/dL*

- Automatic dispatch of subject educational materials (twice weekly)

**[Control Group]**

For the control group, the basic usage of the 'Well Check' smartphone application is recommended as follows. Subjects are encouraged to use the 'Well Check' app in a self-recording format. The investigator will not monitor or utilize the subject's use of 'Well Check' during the study period.

1. Visit 1 (Baseline, Day 0) to Visit 5 (Close-out Visit, 24 weeks)

- No specific guidance or settings for the 'Well Check' application are provided; subjects use it freely for self-recording
- Investigator (Responsible Physician): No separate management or consultation via 'Well Check Doctor Web'; routine medical care is provided
- Automatic dispatch of subject educational materials (twice weekly)

1. **Demographic Information**

At Visit 1 (Baseline, Day 0), the following information is collected to verify the subject's basic information. Pregnancy status is collected through interview or existing pregnancy test results, if available.

- Initials
- Gender
- Month and year of birth, age
- Pregnancy and breastfeeding status

1. **Information on Type 2 Diabetes**

Collect the diagnosis date of type 2 Diabetes at Visit 1 (Baseline, Day 0).

1. **Medical History Review**

For medical history, any clinically significant medical conditions or abnormalities observed before Visit 1 (Baseline, Day 0), excluding the target disease, will be defined. The diagnosis name and date of each condition will be collected for medical history within 6 months prior to Visit 1 (Baseline, Day 0) and ongoing conditions.

1. **Alcohol/Smoking/Lifestyle Information**

At Visit 1 (Baseline, Day 0), the following information is collected to verify the subject's basic information, and any changes will be additionally collected at each subsequent visit. Verify through routine medical visits, medical records, and for the test group, data collected within the 'Well Check' application can be utilized.

1. Drinking history
   - Current Drinker*: ≥ 12 glasses (units) in a lifetime and drinking at least once in the last 12 months
   - Former Drinker: Has consumed at least 12 units of alcohol in their lifetime but has not drunk in the past 12 months
   - Non-Drinker: < 12 glasses (units) in a lifetime

^*^ For current drinkers, the weekly drinking frequency and amount per occasion will be confirmed.

1. Smoking history
   - Current Smoker: Has smoked ≥ 5 packs (100 cigarettes) in a lifetime and smoked within the past 30 days
   - Former Smoker: Has smoked ≥ 5 packs (100 cigarettes) in a lifetime, but no smoking in the last 30 days
   - Non-smoker: Has smoked < 5 packs (100 cigarettes) in a lifetime
2. Lifestyle Habits (Dietary Habits): Irregular meals, overeating, excessive intake of carbohydrate/sugar, excessive fat intake, excessive salt intake
3. Lifestyle Habits (Exercise Habits): Types of exercise (walking, aerobic exercise, strength training), weekly exercise frequency, exercise intensity (less than 30 minutes, up to 1 hour, long duration)
4. **Physical Measurement**

Collect weight and BMI at every visit, with BMI automatically calculated in the CRF using height and weight. Collect height once at Visit 1 (Baseline, Day 0).

1. **Vital Signs**

At every visit, the following vital signs will be collected:

- Blood pressure (systolic/diastolic)
- Pulse Rate

Blood pressure and pulse rate should be measured in a quiet environment after at least 5 minutes of rest in a chair with a backrest. The subject should refrain from smoking, alcohol, and caffeine intake for at least 30 minutes prior to measurement, if possible.

1. **Body Composition Analysis**

For the feasible institutions capable of conducting these measurements, collect the following items at Visit 1 (Baseline, Day 0), Visit 3 (Follow-up visit, 12 weeks), and Visit 5 (Close-out visit, 24 weeks).

- Body composition analyzer indices: Skeletal muscle mass, body fat mass, body fat percentage, muscle mass, waist/hip circumference, body water, intracellular water, extracellular water, extracellular water ratio, abdominal fat percentage, etc.

1. **Prior/Concomitant Medications**

For prior medications, collect information on diabetes treatments administered within 4 weeks before Visit 1 (Baseline, Day 0). For concomitant medications, collect information on all concomitant medications taken for 3 months or more during the study period after Visit 1 (Baseline, Day 0), including those for the treatment of Type 2 Diabetes.

- Drug Name (Brand Name)
- Dosage and Administration (Dose per administration, unit, frequency, route)
- Duration of Administration (Start date, end date, ongoing status)
- Purpose of Administration
- Reason for Dose Adjustment or Discontinuation (if applicable)

1. **Laboratory Tests**

Laboratory tests are collected based on standard clinical procedures in a real-world clinical setting. If there are HbA1c results within 4 weeks prior to Visit 1 (Baseline, Day 0) or other test results collected within 3 months, these results can be used as substitutes for the laboratory tests at Visit 1 (Baseline, Day 0).

Cardiovascular disease complication risk (Atherosclerotic Cardiovascular Disease risk, ASCVD risk) will be assessed using the ASCVD 2013 Risk Calculator from AHA/ACC. Analysis will be conducted after the study is completed based on information collected in the eCRF (gender, age, systolic blood pressure, total cholesterol, HDL-C, hypertension medication use, diabetes diagnosis, and smoking status). For the test group, the automatic calculation feature within the Well Check app allows investigators (responsible physicians) to input cholesterol and blood pressure values for use during patient consultations.

Examples of Laboratory Test Items to be Collected:

| Main Laboratory Tests | HbA1c, FPG |
| --- | --- |
| Other Laboratory Tests | Total Cholesterol, HDL-C, LDL-C, Triglyceride, ALT, AST, γ-GTP, Creatinine, e GFR, UACR, UGCR |

1. **Well Check Usage Satisfaction Survey**

The satisfaction survey on the usage experience of 'Well Check' by both medical staff and subjects will be conducted in writing during Visit 5 (Close-out Visit, Week 24).

The survey consists of 10 questions and 5 scales designed to evaluate satisfaction with the use of the 'Well Check' application. It is a general survey aimed at assessing the effectiveness of chronic disease management and improvement in work efficiency due to the application usage, rather than targeting any specific disease group.

The 10 questions of Medical Staff Satisfaction Survey aim to assess the effectiveness of managing patients with chronic diseases and the improvement in work efficiency due to the use of the application. The 5-point scale consists of 1) Strongly Disagree 2) Disagree 3) Neutral 4) Agree 5) Strongly Agree

The 10 questions of Subject Satisfaction Survey aim to assess the satisfaction with the relationship with medical staff and the helpfulness of the treatment process experience due to the use of the application. The 5-point scale consists of 1) Strongly Disagree 2) Disagree 3) Neutral 4) Agree 5) Strongly Agree

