| **Clinical Study Design and Methods** | This clinical study is designed as a primary care-based, prospective, multicenter, cluster-randomized, pragmatic clinical trial to confirm the improvement effects on blood glucose, blood pressure, and weight over 24 weeks in patients with Type 2 Diabetes when using ‘Well Check’ with or without investigator-linked management in real-world primary care settings.  Patients with Type 2 Diabetes, who, based on the medical judgment of the investigator (responsible physician), have no difficulty using the digital healthcare mobile application on their smartphones, will be recruited in real-world practice settings.  To confirm the clinical basis of ‘Well Check,’ a prospective, multicenter clinical study will be conducted. However, considering the practical constraints of primary care settings where it is difficult to clearly distinguish test groups from control groups within the same institution, a 1:1 cluster randomization will be employed. This will divide study institutions into those administering to the test group (group using ‘Well Check’ with investigator (responsible physician)-linked management) and those administering to the control group (group using ‘Well Check’ for simple self-management).  This clinical study will collect demographic information, physical measurement, vital signs, and laboratory test results up to 24 weeks after starting the use of ‘Well Check’ in real-world clinical settings. Data will be collected based on medical records documented in real-world clinical settings and data gathered through ‘Well Check.’ There are no mandatory visits, tests, or treatments specifically required by this clinical study.  However, follow-up visits will be conducted to prospectively collect efficacy and safety evaluation data at approximately 6 weeks (±2 weeks), 12 weeks (±2 weeks), 18 weeks (±2 weeks), and 24 weeks (±2 weeks) from the date of subject enrollment (baseline, Day 0). The collected items include basic clinical information such as age, gender, past and current medical history, lifestyle habits (smoking, alcohol consumption, physical activity), previous and concomitant medications, and clinical indicators such as weight, body mass index (BMI), body fat mass (optional via body composition analyzer), fasting blood glucose, glycated hemoglobin (HbA1c), blood pressure (systolic/diastolic), total cholesterol, LDL cholesterol, HDL cholesterol, triglycerides, liver function tests (AST, ALT, γ-GTP), and safety evaluation parameters such as vital signs and laboratory tests. During the study, the investigator will collect the necessary data based on the information gathered during routine clinical care.  Participating Institutions  (Primary Care Institutions)  Cluster Randomization  Investigator  (Responsible Physician)  Use of 'Well Check'  for Integrated Management  (Study Group Institutions)  Study Subjects  Use of 'Well Check'  for Simple Self-Management  (Control Group Institutions)  [figure not shown]<Clinical Study Design>  [figure not shown]  Visit 1  (0 day)  Visit 2  (6±2 weeks)  Visit 3  (12±2 weeks)  Visit 4  (18±2 weeks)  Visit 5  (24±2 weeks)  Baseline  Follow-Up Visits  Close-Out Visit (COV)  <Clinical Study Flowchart> |

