5. For alcohol/smoking/lifestyle habits, data is collected at each visit. For the test group, this can be done through the "pre-visit questionnaire" function within "Well Check" or during consultation with the investigator (responsible physician). For the control group, data is collected through consultation with the investigator (responsible physician e) during visits. Alcohol history includes the frequency of drinking per week and the amount consumed per occasion. Smoking history includes selecting one of the following: current smoker, former smoker, or non-smoker. Lifestyle habits include dietary and exercise habits. Dietary habits can include irregular meals, overeating, excessive intake of carbohydrates/sugars, fats, or salt and multiple items can be selected. Exercise habits include the frequency of exercise per week, type of exercise (walking, aerobic exercise, strength training), and intensity of exercise (less than 30 minutes, less than 1 hour, long duration).
6. Collect physical measurements (height, weight, BMI), with BMI calculated automatically through EDC using height and weight. Height is collected only at Visit 1 (Baseline, Day 0) to the first decimal place.
7. After at least 5 minutes of rest, collect vital signs (systolic blood pressure, diastolic blood pressure, pulse rate). If there are measurement results at each visit, collect these results.
8. Body composition analysis (skeletal muscle mass, body fat mass, body fat percentage, muscle mass, waist/hip circumference, body water, intracellular water, extracellular water, extracellular water ratio, abdominal fat percentage) is conducted at Visit 1 (Baseline, Day 0), Visit 3 (Follow-up visit, 12 weeks), and Visit 5 (Close-out visit, 24 weeks). This variable is measured only in institutions where such measurement is possible and is considered an exploratory clinical variable.
9. - Prior Medications: Collect information on diabetes medications used specifically for the treatment of Type 2 Diabetes within 4 weeks prior to Visit 1 (Baseline, Day 0). This includes the drug name (generic or brand name), duration of administration (start date, end date, ongoing status), single dose amount/unit, daily administration frequency, and route of administration.

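### Smoking and lifestyle data may come from the app in the test arm only, which reaches the exploratory ASCVD risk endpoint; the source of visit BP and weight is left unclear

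*Protocol*

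**What the plan says.** Two places set the source of alcohol, smoking and lifestyle data.

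- Schedule for Data Collection, footnote 5: "For alcohol/smoking/lifestyle habits, data is collected at each visit. For the test group, this can be done through the" app's pre-visit questionnaire, or in consultation. The footnote continues: "For the control group, data is collected through consultation with the investigator" at visits.
- Section 4.4, Alcohol/Smoking/Lifestyle Information: sites check these items from ordinary visits and the chart "and for the test group, data collected within the" app.

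Two other places set the source of study data in general. Both follow a list that includes physical measurements, vital signs and laboratory results.

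- Synopsis, Clinical Study Design and Methods: "Data will be collected based on medical records documented in real-world clinical settings and data gathered through" Well Check.
- Section 4.1: "Data collection for this clinical study will be based on medical records documented during routine clinical visits". The app is not named.

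The arms also differ in what the physician may do with app records. Section 4.4 has the test-arm physician review self-recorded BP and weight from Visit 2 to Visit 5. For the control arm it says: "The investigator will not monitor or utilize the subject's use of" the app during the study.

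**The concern.** In a comparison between arms, an outcome or its inputs should be obtained the same way in both. A patient filling in a questionnaire on a phone may report smoking differently from one answering a physician face to face. If the first route is open in one arm only, part of any difference in ASCVD risk may reflect how the question was asked.

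The same question arises for BP and weight. These are secondary endpoints, and section 4.1 names both among the effects the study is to confirm. If home readings stood in for clinic readings in one arm only, the arms would differ in place, device and assessor. The analysis could not undo this unless the source of each value had been recorded.

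**Working it through.** The protocol gives no figure on this point, so there is none to reproduce. The check sets the source rules side by side.

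**1. Smoking, alcohol and lifestyle.** Test arm: app questionnaire or app data, or consultation (footnote 5, section 4.4). Control arm: consultation (footnote 5). The difference between arms is stated. In the test arm the app is allowed but not required, so the source may vary between subjects and between visits of one subject. Section 4.4 defines current, former and non-smoker, but the protocol does not say that the app questionnaire uses those definitions.

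**2. Does it reach an endpoint?** Smoking, alcohol and lifestyle are not endpoints. Smoking status is, however, an input to ASCVD risk (section 4.4, Laboratory Tests), which is exploratory at weeks 12 and 24 (section 7.1). The calculation is done after the study from eCRF data with one calculator for both arms. That makes the formula equal, not the way its smoking input was obtained.

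**3. Does change from baseline remove it?** Not reliably. Test-arm subjects complete an app questionnaire at Visit 1, so the app may be the source both at baseline and later, and a constant reporting difference would then cancel. Because the source may switch between visits, this is not assured. The direction of any bias cannot be predicted.

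**4. BP and weight.** Section 4.4 has one rule for both arms. BP is taken seated and rested in a quiet place; weight is collected at every visit, with no condition on place or device. No arm-specific source is given. What leaves the matter open is a combination of four things:

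- The synopsis names app data as a source directly after listing physical measurements and vital signs; section 4.1 does not.
- Test-arm subjects are asked to record BP and weight in the app at least weekly, and their physician reviews these entries; the control-arm investigator does not use the app.
- Visits 2 and 4 may be held by phone, where no clinic reading is possible, yet section 7.1 lists BP, weight and BMI at weeks 6 and 18.
- Nothing forbids entering an app reading as a visit value.

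Baseline would probably be a clinic reading in both arms, because section 3.4 excludes prior users and the app is installed at Visit 1.

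**5. Size.** Let f be the share of test-arm follow-up values taken from the app, and d the mean difference between app and clinic values. With clinic values at baseline and throughout the control arm, the spurious difference between arms is f × d. The documents give neither f nor d. As no passage provides for entering app BP or weight, f may be 0; its upper limit is 1. The result runs from 0 × d = 0 to 1 × d = d, with d unknown.

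**The case against.** The case on the other side is strong for BP and weight. Where the protocol lets test-arm sites use app data, it says so, and it does so only for alcohol, smoking and lifestyle. The measurement rule for vital signs is common to both arms. Review of home entries is described as part of the intervention, not as a step in filling the eCRF. The synopsis wording is not specific to an arm and could refer only to items that do come from the app, such as login days and the test-arm questionnaires. Phone visits are allowed in both arms, and control subjects self-record too, so they could read out home values as well.

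Most of this stands. A reader might infer that BP and weight are measured by different methods in the two arms, and that a false benefit of some mmHg or kg follows. The documents do not support that. No passage tells sites to enter home readings, and any such figure would rest wholly on assumed inputs. What remains is that the synopsis and section 4.1 differ on the source of these data and that no rule settles it.

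For smoking, the objection is about reach. ASCVD risk is exploratory, its weeks 12 and 24 are not the optional phone visits, and smoking is self-reported in both arms. This limits the importance of the point. It does not remove the stated difference in source.

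**Conclusion.** The point holds in two parts of different strength.

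- **Stated in the text:** smoking, alcohol and lifestyle data may come from the app in the test arm and come from consultation in the control arm. Through smoking status, a difference in ascertainment can affect ASCVD risk at weeks 12 and 24. The documented path reaches this one exploratory endpoint.
- **Left open by the text:** whether home BP and weight may be entered as visit values, which in practice would be easier in the test arm. This is a possible reading, most relevant at phone visits. If it happened, it would reach secondary endpoints and, through systolic BP, ASCVD risk.

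Neither effect can be sized or signed from the documents. The primary endpoint is HbA1c, a laboratory value, and is not affected. The point is minor for the trial's main conclusion, but worth correcting because differing sources cannot be separated later unless they were recorded.

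**What to change.** 1. In footnote 5 and section 4.4, collect smoking, alcohol and lifestyle with the same consultation questions in both arms, using the section 4.4 categories. Use that answer for ASCVD risk. The pre-visit questionnaire can stay as part of the test-arm intervention.
2. Reconcile the synopsis with section 4.1. State that endpoint BP and weight are clinic measurements at the visit in both arms, and that app records are not entered as visit values. If the sponsor wishes to keep other sources, the minimum is an eCRF field giving the source of each value.

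This takes protocol and eCRF-guideline wording. The cost is a few questions asked in person in the test arm, and no endpoint BP or weight at visits held by phone, which thins the week 6 and week 18 data.
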